**4.2 Supportive Care Guidelines**

**4.2.1 Growth Factors**

Hematological growth factors will not be used prophylactically in this study, but may be used at the discretion of the investigator in the event of severe hematological toxicity.

**4.2.3 Contraception**

Women of childbearing potential and sexually active males are strongly advised to use an effective method of contraception.

- - 1. **Other**

Other appropriate supportive care medications may be administered at the investigator’s discretion. . In the event of hand-foot syndrome, patients may use topical emollients (such as Aquaphor), topical steroids, and/or anti-histamines for symptom relief.

**4.3 Duration of Therapy**

In the absence of treatment delays due to adverse event(s), treatment may continue until one of the following criteria applies:

- Disease progression,
- Intercurrent illness that prevents further administration of treatment,
- Unacceptable adverse event(s)
- Patient decides to withdraw from the study
- General or specific changes in the patient’s condition render the patient unacceptable for further treatment in the judgment of the investigator.
- If GI-Perforation (NOS), patients must be taken off therapy

1. **EXPECTED ADVERSE EVENTS / DOSE MODIFICATIONS**

5.1

- 1. **Expected Adverse Events Associated with BAY 43-9006**

**Comprehensive Adverse Events and Potential Risks List (CAEPR)**

**for**

**Sorafenib (BAY 43-9006, NSC 724772)**

The Comprehensive Adverse Event and Potential Risks list (CAEPR) provides a single, complete list of reported and/or potential adverse events (AE) associated with an agent using a uniform presentation of events by body system. In addition to the comprehensive list, a subset, the Agent Specific Adverse Event List (ASAEL), appears in a separate column and is identified with ***bold*** and ***italicized*** text. This subset of AEs (ASAEL) contains events that are considered 'expected' for expedited reporting purposes only. Refer to the 'CTEP, NCI Guidelines: Adverse Event Reporting Requirements' http://ctep.cancer.gov/reporting/adeers.html for further clarification. *Frequency is provided based on 1376 patients*. Below is the CAEPR for sorafenib.

**Comprehensive Adverse Events and Potential Risks List (CAEPR)**

**for**

**Sorafenib (BAY 43-9006, NSC 724772)**

The Comprehensive Adverse Event and Potential Risks list (CAEPR) provides a single list of reported and/or potential adverse events (AE) associated with an agent using a uniform presentation of events by body system. In addition to the comprehensive list, a subset, the Agent Specific Adverse Event List (ASAEL), appears in a separate column and is identified with ***bold*** and ***italicized*** text. This subset of AEs (ASAEL) contains events that are considered 'expected' for expedited reporting purposes only. Refer to the 'CTEP, NCI Guidelines: Adverse Event Reporting Requirements' http://ctep.cancer.gov/reporting/adeers.html for further clarification. *Frequency is provided based on 1376 patients*. Below is the CAEPR for sorafenib.

**Version 2.1, June 23, 20061**

| **Adverse Events with Possible**  **Relationship to Sorafenib (BAY 43-9006)**  **(CTCAE v3.0 Term)**  **[n=1376 patients]** | | | **'Agent Specific Adverse Event List'**  **(ASAEL)** |
| --- | --- | --- | --- |
| **Likely (>20%)** | **Less Likely (<=20%)** | **Rare but Serious (<3%)** |
| ALLERGY/IMMUNOLOGY | | | |
|  | Allergic reaction/hypersensitivity (including drug fever) |  |  |
| BLOOD/BONE MARROW | | | |
|  | Hemoglobin |  |  |
|  | Leukocytes (total WBC) |  |  |
|  | Lymphopenia |  |  |
|  | Neutrophils/granulocytes (ANC/AGC) |  |  |
|  | Platelets |  |  |
| CARDIAC GENERAL | | | |
|  | Hypertension |  | ***Hypertension*** |
| CONSTITUTIONAL SYMPTOMS | | | |
| Fatigue (asthenia, lethargy, malaise) |  |  | ***Fatigue (asthenia, lethargy, malaise)*** |
|  | Fever (in the absence of neutropenia, where neutropenia is defined as ANC <1.0 x 10e9/L) |  |  |
|  | Rigors/chills |  |  |
|  | Weight loss |  |  |
| DERMATOLOGY/SKIN | | | |
|  | Dermatology/Skin - Other (non-life threatening squamous cell carcinoma of skin: keratoacanthoma type) |  |  |
|  | Dermatology/Skin - Other (other) |  |  |
|  | Dry skin |  |  |
|  | Flushing |  |  |
|  | Hair loss/alopecia (scalp or body) |  |  |
|  | Hypopigmentation |  |  |
|  | Nail changes |  |  |
|  | Pruritus/itching |  |  |
| Rash/desquamation |  |  | ***Rash/desquamation*** |
| Rash: hand-foot skin reaction |  |  | ***Rash: hand-foot skin reaction*** |
| GASTROINTESTINAL | | | |
|  | Anorexia |  |  |
|  | Ascites (non-malignant) |  |  |
|  | Constipation |  |  |
|  | Dehydration |  |  |
| Diarrhea |  |  | ***Diarrhea*** |
|  | Dysphagia (difficulty swallowing) |  |  |
|  | Flatulence |  |  |
|  | Heartburn/dyspepsia |  |  |
|  | Mucositis/stomatitis (functional/symptomatic): pharynx |  |  |
|  | Nausea |  |  |
|  |  | Perforation, GI - NOS |  |
|  | Vomiting |  |  |
| HEMORRHAGE/BLEEDING | | | |
|  | Hemorrhage GI - Select |  |  |
|  | Hemorrhage GU - Select |  |  |
| HEPATOBILIARY/PANCREAS | | | |
|  | Pancreatitis |  |  |
| INFECTION | | | |
|  | Febrile neutropenia (fever of unknown origin without clinically or microbiologically documented infection)(ANC <1.0 x 10e9/L, fever >=38.5 degrees C) |  |  |
|  | Infection with unknown ANC - Select |  |  |
| METABOLIC/LABORATORY | | | |
|  | Albumin, serum-low (hypoalbuminemia) |  |  |
|  | Alkaline phosphatase |  |  |
|  | ALT, SGPT (serum glutamic pyruvic transaminase) |  |  |
|  | Amylase |  |  |
|  | AST, SGOT (serum glutamic oxaloacetic transaminase) |  |  |
|  | Bilirubin (hyperbilirubinemia) |  |  |
|  | GGT (gamma-glutamyl transpeptidase) |  |  |
|  | Glucose, serum-high (hyperglycemia) |  |  |
|  | Lipase |  |  |
|  | Metabolic/Laboratory - Other (blood elastase) |  |  |
|  | Phosphate, serum-low (hypophosphatemia) |  |  |
| NEUROLOGY | | | |
|  | Neuropathy: sensory |  |  |
| PAIN | | | |
|  | Pain - abdomen NOS |  |  |
|  | Pain - joint |  |  |
|  | Pain - muscle |  |  |
|  | Pain NOS |  |  |
| PULMONARY/UPPER RESPIRATORY | | | |
|  | Hypoxia |  |  |
|  | Pleural effusion (non-malignant) |  |  |
|  | Pneumonitis/pulmonary infiltrates |  |  |
|  | Pneumothorax |  |  |
| RENAL/GENITOURINARY | | | |
|  | Renal failure |  |  |
| SYNDROMES | | | |
|  | Flu-like syndrome |  |  |

**1**This table will be updated as the toxicity profile of the agent is revised. Updates will be distributed to all Principal Investigators at the time of revision. The current version can be obtained by contacting [contact]. Your name, the name of the investigator, the protocol and the agent should be included in the e-mail.

**Also reported on BAY 43-9006 trials but with the relationship to BAY 43-9006 still undetermined:**

**ALLERGY/IMMUNOLOGY** - linear IgA disease

**CARDIAC ARRHYTHMIA** - atrial flutter; supraventricular arrhythmia

**CARDIAC GENERAL** - cardiac ischemia/infarction; left ventricular systolic dysfunction

**COAGULATION** - INR; PTT; thrombotic microangiopathy

**DERMATOLOGY/SKIN** - erythema multiforme

**GASTROINTESTINAL** - ileus

**HEMORRHAGE/BLEEDING** - CNS hemorrhage; petechiae; pleural hemorrhage; splenic infarction

**LYMPHATICS** - limb edema

**METABOLIC/LABORATORY** - creatinine; hyperuricemia; hyponatremia

**MUSCULOSKELETAL/SOFT TISSUE** - arthritis

**NEUROLOGY** - anxiety; CNS ischemia; dizziness; encephalopathy; memory impairment; psychosis; syncope

**OCULAR/VISUAL** - diplopia; uveitis

**PAIN** - back pain; bone pain; chest/thorax pain; headache; limb pain

**PULMONARY/UPPER RESPIRATORY** - ARDS; dyspnea; voice changes

**SEXUAL/REPRODUCTIVE FUNCTION** - erectile dysfunction

**VASCULAR** - thrombosis/thrombus/embolism

**Note**: BAY 43-9006 in combination with other agents could cause an exacerbation of any adverse event currently known to be caused by the other agent, or the combination may result in events never previously associated with either agent.

**Version 2.0, February 22, 20061**

| **Adverse Events with Possible**  **Relationship to Sorafenib (BAY 43-9006)**  **(CTCAE v3.0 Term)**  **[n=1376 patients]** | | | | | | **'Agent Specific Adverse Event List'**  **(ASAEL)** |
| --- | --- | --- | --- | --- | --- | --- |
| **Likely (>20%)** | | **Less Likely (<=20%)** | **Rare but Serious (<3%)** | | |
| ALLERGY/IMMUNOLOGY | | | | | | |
|  | | Allergic reaction/hypersensitivity (including drug fever) |  | | |  |
| BLOOD/BONE MARROW | | | | | | |
|  | Hemoglobin | |  | |  | |
|  | Leukocytes (total WBC) | |  | |  | |
|  | Lymphopenia | |  | |  | |
|  | Neutrophils/granulocytes (ANC/AGC) | |  | |  | |
|  | Platelets | |  | |  | |
| CARDIAC GENERAL | | | | | | |
|  | | Hypertension | |  | | ***Hypertension*** |
| CONSTITUTIONAL SYMPTOMS | | | | | | |
| Fatigue (asthenia, lethargy, malaise) | |  | |  | | ***Fatigue (asthenia, lethargy, malaise)*** |
|  | | Fever (in the absence of neutropenia, where neutropenia is defined as ANC <1.0 x 10e9/L) | |  | |  |
|  | | Rigors/chills | |  | |  |
|  | | Weight loss | |  | |  |
| DERMATOLOGY/SKIN | | | | | | |
|  | | Dry skin | |  | |  |
|  | | Flushing | |  | |  |
|  | | Hair loss/alopecia (scalp or body) | |  | |  |
|  | | Hypopigmentation | |  | |  |
|  | | Nail changes | |  | |  |
|  | | Pruritus/itching | |  | |  |
| Rash/desquamation | |  | |  | | ***Rash/desquamation*** |
| Rash: hand-foot skin reaction | |  | |  | | ***Rash: hand-foot skin reaction*** |
|  | | Dermatology/skin – Other: non-life threatening squamous cell carcinoma of the skin: keratoacanthoma type | |  | |  |
| GASTROINTESTINAL | | | | | | |
|  | | Anorexia | |  | |  |
|  | | Ascites (non-malignant) | |  | |  |
|  | | Constipation | |  | |  |
|  | | Dehydration | |  | |  |
| Diarrhea | |  | |  | | ***Diarrhea*** |
|  | | Dysphagia (difficulty swallowing) | |  | |  |
|  | | Flatulence | |  | |  |
|  | | Heartburn/dyspepsia | |  | |  |
|  | | Mucositis/stomatitis (functional/symptomatic): pharynx | |  | |  |
|  | | Nausea | |  | |  |
|  | | Vomiting | |  | |  |
| HEMORRHAGE/BLEEDING | | | | | | |
|  | | Hemorrhage GI - Select | |  | |  |
|  | | Hemorrhage GU - Select | |  | |  |
| HEPATOBILIARY/PANCREAS | | | | | | |
|  | | Pancreatitis | |  | |  |
| INFECTION | | | | | | |
|  | | Febrile neutropenia (fever of unknown origin without clinically or microbiologically documented infection)(ANC <1.0 x 10e9/L, fever >=38.5 degrees C) | |  | |  |
|  | | Infection with unknown ANC-Select | |  | |  |
| METABOLIC/LABORATORY | | | | | | |
|  | | Albumin, serum-low (hypoalbuminemia) | |  | |  |
|  | | Alkaline phosphatase | |  | |  |
|  | | ALT, SGPT (serum glutamic pyruvic transaminase) | |  | |  |
|  | | Amylase | |  | |  |
|  | | AST, SGOT (serum glutamic oxaloacetic transaminase) | |  | |  |
|  | | Bilirubin (hyperbilirubinemia) | |  | |  |
|  | | GGT (gamma-glutamyl transpeptidase) | |  | |  |
|  | | Glucose, serum-high (hyperglycemia) | |  | |  |
|  | | Phosphate, serum-low (hypophosphatemia) | |  | |  |
|  | | Lipase | |  | |  |
|  | | Metabolic/Laboratory - Other (blood elastase) | |  | |  |
| NEUROLOGY | | | | | | |
|  | | Neuropathy: sensory | |  | |  |
| PAIN | | | | | | |
|  | | Pain - abdomen NOS | |  | |  |
|  | | Pain - joint | |  | |  |
|  | | Pain - muscle | |  | |  |
|  | | Pain NOS | |  | |  |
| PULMONARY/UPPER RESPIRATORY | | | | | | |
|  | | Hypoxia | |  | |  |
|  | | Pleural effusion (non-malignant) | |  | |  |
|  | | Pneumonitis/pulmonary infiltrates | |  | |  |
|  | | Pneumothorax | |  | |  |
| RENAL/GENITOURINARY | | | | | | |
|  | | Renal failure | |  | |  |
| SYNDROMES | | | | | | |
|  | | Flu-like syndrome | |  | |  |

**1**This table will be updated as the toxicity profile of the agent is revised. Updates will be distributed to all Principal Investigators at the time of revision. The current version can be obtained by contacting [contact]. Your name, the name of the investigator, the protocol and the agent should be included in the e-mail.

**Also reported on sorafenib trials but with the relationship to sorafenib still undetermined:**

**ALLERGY/IMMUNOLOGY** - linear IgA disease

**CARDIAC ARRHYTHMIA** - atrial flutter; supraventricular arrhythmia

**CARDIAC GENERAL** - cardiac ischemia/infarction; left ventricular systolic dysfunction

**COAGULATION** - INR; PTT; thrombotic microangiopathy

**DERMATOLOGY/SKIN** – erythema multiforme

**GASTROINTESTINAL** - ileus

**HEMORRHAGE/BLEEDING** - CNS hemorrhage; petechiae; pleural hemorrhage; splenic infarction

**LYMPHATICS** - limb edema

**METABOLIC/LABORATORY** - creatinine; hyperuricemia; hyponatremia

**MUSCULOSKELETAL/SOFT TISSUE** - arthritis

**NEUROLOGY** - anxiety; CNS ischemia; dizziness; encephalopathy; memory impairment; psychosis; syncope

**OCULAR/VISUAL** - diplopia; uveitis

**PAIN** - back pain; bone pain; chest/thorax pain; headache; limb pain

**PULMONARY/UPPER RESPIRATORY** - ARDS; dyspnea; voice changes

**SEXUAL/REPRODUCTIVE FUNCTION –** erectile dysfunction

**VASCULAR** - thrombosis/thrombus/embolism

**Note**: Sorafenib in combination with other agents could cause an exacerbation of any adverse event currently known to be caused by the other agent, or the combination may result in events never previously associated with either agent.

**5.2 Dosing Delays / Dose Modifications**

Prior to re-treatment, patients must have recovered the following organ function:

- absolute neutrophil count 1.0 x 109/l
- platelets 100 x 109/l
- total bilirubin < 2 x upper limit of normal
- AST (SGOT) / ALT (SGPT) 2.5 x upper limit of normal
- creatinine 1.5 x upper limit of normal
- other Grade 0-1
- Patients should be dose reduced to 400mg po in AM and 200mg po in PM in the event of any of the following:
- Nausea or vomiting dose reductions should only be in the face of maximal anti-emetic therapy
- Grade 4 non-hematologic toxicity: if study drug related patients should be taken off study
- Grade 3 non-hematologic toxicity: hold BAY43-9006 and reevaluate patient weekly until toxicity improves to < Grade 1. Reduce dose by 200 mg /day and no more than 2 dose reductions allowed.
- Increased liver functions (Grade 3-4): withhold treatment until resolved to < grade 1 toxicity and decrease by 200 mg.
- Grade 4 hematologic toxicity: withhold treatment until resolvedto < grade 1 toxicity and decrease by 200 mg. If Grade 4 neutropenia lasts for more than 7 days after therapy with growth factor support contact PI.
- Many patients will have a rash that will require drug withdrawal and toxicity resolution before restarting. Hand-foot syndrome will require drug withdrawal and reduction

Management of Treatment-emergent Hypertension:

| **Grade of Event (CTCAE v.3)** | **Management/ Next Dose** |
| --- | --- |
| grade 1 | Consider increased BP monitoring |
| grade 2 asymptomatic and diastolic BP < 110 mm Hg | Begin anti-hypertensive therapy and continue agent |
| grade 2 symptomatic/ persistent  OR  diastolic BP ≥ 110 mm Hg  OR  grade 3 | 1. Agent should be held* until symptoms resolve  and diastolic BP ≤ 100 mm Hg; also  treat patient with anti-hypertensives and when  agent is restarted, reduce by 1 dose level.**  2. If diastolic BP not controlled (≤ 100) on  therapy, reduce another dose level *** |
| grade 4 | Discontinue protocol therapy |
| * Patients requiring a delay of > 2 weeks should go off protocol therapy.  ** May be able to resume full dose later.  *** Patients requiring > 2 dose reductions should go off protocol therapy. | |

Current CTCAE definitions used by CTEP:

Grade 1: asymptomatic, transient (< 24 hours) increase by > 20 mmHg (diastolic) or to

>150/100 if previously WNL; intervention not indicated

Grade 2: recurrent or persistent (> 24 hours) or symptomatic increase by > 20 mmHg

(diastolic) or to > 150/100 if previously WNL; monotherapy may be indicated

Grade 3: requiring more than one drug or more intensive therapy than previously

Grade 4: life threatening (e.g. hypertensive crisis)

Patients will be allowed 3 weeks for resolution of toxicity. Treatment will be discontinued if any grade 3 or 4 toxicity does not resolve in 3 weeks.

No patients should have his / her dose re-escalated following dose reduction.

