**Note:**

- Patients with a global deterioration of health status requiring discontinuation of treatment without objective evidence of disease progression at that time should be classified as having “symptomatic deterioration.” Every effort should be made to document the objective progression, even after discontinuation of treatment.
- In some circumstances, it may be difficult to distinguish residual disease from normal tissue. When the evaluation of complete response depends on this determination, it is recommended that the residual lesion be investigated (fine needle aspirate/biopsy) before confirming the complete response status.

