**11.4 Analysis of Secondary Endpoints**

All patients will be followed for progression and survival. Kaplan-Meier estimates will be calculated for time to progression and overall survival, and medians, along with two-sided 95% confidence intervals, will be reported.

All adverse events without regard to causal relationship and by causal relationship to study drugs will be summarized.

Exploratory analyses of correlative endpoints will be examined over time using descriptive statistics and graphical displays. In particular, these endpoints will also be explored in relation to response to treatment and tumor burden.

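### Section 5.2 takes patients with drug-related grade 4 non-hematologic toxicity off study, while every other toxicity stop is worded as ending therapy; read literally, this conflicts with follow-up in 11.4

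*Protocol*

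**What the plan says.** Section 5.2 (Dosing Delays / Dose Modifications) has one bullet for this event: "Grade 4 non-hematologic toxicity: if study drug related patients should be taken off study".

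The other toxicity stops use different words:

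- Grade 4 hypertension (5.2, hypertension table): "Discontinue protocol therapy".
- Long hypertension delays (5.2, table footnote): "Patients requiring a delay of > 2 weeks should go off protocol therapy". The footnote on more than two dose reductions uses the same term.
- Unresolved toxicity (end of 5.2): "Treatment will be discontinued if any grade 3 or 4 toxicity does not resolve in 3 weeks".
- GI perforation (4.3, Duration of Therapy): "If GI-Perforation (NOS), patients must be taken off therapy".

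On follow-up, section 11.4 says "All patients will be followed for progression and survival" and "Kaplan-Meier estimates will be calculated for time to progression and overall survival". Section 9.5 runs TTP from the first treatment day to the first documented progression and makes no reference to being on drug. The note under 9.3.3, on patients who stop with symptomatic deterioration, adds: "Every effort should be made to document the objective progression, even after discontinuation of treatment".

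**The concern.** Leaving therapy and leaving study differ in their statistical consequences. A patient who leaves therapy is still scanned and contacted. A patient who leaves the study is not, and is censored in a Kaplan-Meier analysis. The 5.2 bullet ties that second outcome to an event caused by the drug. Patients with severe drug toxicity may well differ in prognosis from those still followed, so such censoring could be informative.

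The rules also overlap. Drug-related grade 4 hypertension is a grade 4 non-hematologic toxicity, so the bullet and the table both apply to it. Drug-related grade 4 GI perforation falls under both the bullet and 4.3. In each case one text says study and the other says therapy, and a site cannot tell whether the difference is intended.

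This concerns site conduct. An analysis plan can set a censoring rule, but it cannot recover scans or survival contacts that were never made.

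**Working it through.** **1. The texts compared.**

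| Event | Section | What the patient leaves |
| --- | --- | --- |
| Drug-related grade 4 non-hematologic toxicity | 5.2 bullet | study |
| Grade 4 hypertension | 5.2 table | protocol therapy |
| Hypertension: delay over 2 weeks, or more than 2 reductions | 5.2 table footnotes | protocol therapy |
| Grade 3 or 4 toxicity unresolved at 3 weeks | 5.2 end | treatment |
| GI perforation | 4.3 | therapy |

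The bullet is the only toxicity stop worded as leaving the study. Section 11.4 makes no exception for such patients. Taken literally, the two cannot both be followed.

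**2. How many patients.** The documents give no rate of drug-related grade 4 non-hematologic events. The single-agent melanoma study at 400 mg BID described in section 2.2 (20 patients) mentions none. If that means 0 of 20, which is an assumption, the exact 95% upper limit is 1 − 0.025^(1/20) = 0.168. With 2 × 37 = 74 patients, that is 0.168 × 74 ≈ 12. Assumed rates of 2%, 5% and 10% give 1.5, 3.7 and 7.4 patients.

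**3. Size of the censoring bias (illustration only).** The base medians come from the DTIC-based phase 3 trial in 2.1.1: 2.6 months to treatment failure, as a stand-in for TTP, and 9.1 months survival. Assumptions:

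- Times are exponential with λ = ln 2 / median.
- A share f is due to have the event at a time U, uniform on 0–84 days (2.76 months).
- The hazard becomes hλ after U.

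Censoring at U, Kaplan-Meier estimates exp(−λt), so the reported median is the base median. Full follow-up would give

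S(t) = (1 − f)·exp(−λt) + f·E[exp(−λ·min(t,U) − hλ·max(t − U, 0))].

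Solving S(t) = 0.5 with h = 2:

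| f | TTP, full follow-up | Overstated by | Survival, full follow-up | Overstated by |
| --- | --- | --- | --- | --- |
| 2% | 2.581 | 0.02 | 8.984 | 0.12 |
| 5% | 2.552 | 0.05 | 8.814 | 0.29 |
| 10% | 2.507 | 0.09 | 8.538 | 0.56 |
| 16.8% | 2.448 | 0.15 | 8.18 | 0.92 |

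All figures are in months. With h = 0.5 and f = 10%, the full-follow-up medians are 2.672 and 9.573, so the reported values would be 0.07 and 0.47 months too short. For scale, an approximate 95% interval around a 9.1-month median with 74 deaths is 9.1·exp(±1.96/√74) = 7.2 to 11.4 months.

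**4. Response rate.** The plan's design stops at 0 of 13 and rejects the drug at 4 or fewer of 37. The probability of accepting the drug is

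Σ (x = 1 to 13) Bin(x; 13, p) · P[Bin(24, p) > 4 − x].

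At p = 0.05 this is 0.0329 and at p = 0.20 it is 0.8583. Both stated error rates, 3.3% and 14.2%, reproduce. If a share L of responders goes unconfirmed and counts as failures, replace p by p(1 − L):

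- L = 2%: power 0.846
- L = 5%: power 0.826, type I error 0.027
- L = 8.46%: power 0.800

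The error is conservative. It also needs a responder at the first imaging, about day 56, to have the event before the confirming scan 4 weeks later, a window of roughly days 56 to 84.

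**The case against.** The strongest reply is that 'off study' is loose wording for off treatment. The bullet sits in a section about dosing. Section 4.3 lists a patient's withdrawal from the study among the reasons to stop treatment, and the calendar heads its end-of-treatment column 'Off Study'. Section 11.4 is explicit and without exception, and 11.5 requires every included patient to be assessed for response despite treatment deviations. This reply largely stands as to intent. It does not remove the need to correct a sentence that gives a worse result when followed as written.

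It is also fair that the contrast is one of wording. The other stopping rules do not say that therapy ends while follow-up continues; they are silent on follow-up. Grade 4 liver function changes and grade 4 hypertension have rules of their own in 5.2, so the group governed by the bullet alone is smaller than its words suggest.

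Three stronger readings are tempting, and the documents support none of them:

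- *That follow-up is in fact abandoned for these patients.* Sections 9.4.1, 9.5, 11.4 and 11.5 all point to continued assessment.
- *That the calendar ends follow-up, because it has no column after 'Off Study'.* It does not say so. The 56-day interval in 9.4.1 and the commitment in 11.4 imply the later assessments, although 9.4.1 does not expressly say that its interval continues off drug.
- *That the primary endpoint is compromised.* Section 11.5 already counts patients without an assessable response as failures, and the calculation above shows little movement.

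**Conclusion.** The point holds as a minor wording conflict. The 5.2 bullet is the one toxicity stop that removes patients from the study. It overlaps with rules that remove them from therapy, and its literal reading conflicts with 11.4 and does not fit the TTP definition in 9.5. Followed as written, it would censor TTP and survival because of a drug effect.

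The size is small: two secondary endpoints, in a subset whose size the documents do not give. The bias figures show scale only and are not an estimate of harm. They rest on assumed event rates, hazard ratios, exponential times and event window, with base medians from DTIC-based regimens. Even at the 16.8% ceiling, the survival bias of 0.92 months lies within the approximate confidence interval. The response rate and the design's error rates are not materially affected.

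**What to change.** In the 5.2 bullet, replace 'taken off study' with 'taken off protocol therapy', the term the hypertension table already uses. Add that follow-up for progression and survival continues as in 11.4. No stopping rule, sample size or analysis changes, and the cost is one phrase in an amendment.

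As a remark only: when the protocol is next amended, the calendar in section 8 could gain a column for patients off therapy without progression. It would show tumor assessment every 56 days, the confirmatory scan where one is due, and survival status. These are assessments that 9.4.1 and 11.4 already imply.

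### The section 5.2 hypertension table gives two incompatible dosing orders for an asymptomatic grade 2 rise lasting over 24 hours with diastolic BP below 110, and the section contradicts itself on resuming full dose

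*Protocol*

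**What the plan says.** The table on treatment-emergent hypertension in Protocol section 5.2 has four rows. The two middle ones matter here.

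- Row 2 reads "grade 2 asymptomatic and diastolic BP < 110 mm Hg | Begin anti-hypertensive therapy and continue agent".
- Row 3 has three alternative triggers: "grade 2 symptomatic/ persistent", or diastolic BP of 110 mm Hg or more, or grade 3. Its action begins "Agent should be held* until symptoms resolve", and diastolic BP must also be 100 mm Hg or lower. Anti-hypertensives are given, and the drug restarts one dose level lower.

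A footnote to the hold says "Patients requiring a delay of > 2 weeks should go off protocol therapy". A footnote to the reduction says "May be able to resume full dose later".

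The grading definitions follow the table. An asymptomatic rise lasting under 24 hours is grade 1, for which the text says "if previously WNL; intervention not indicated". The next definition begins "Grade 2: recurrent or persistent (> 24 hours) or symptomatic increase by > 20 mmHg".

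Section 5.2 closes with "No patients should have his / her dose re-escalated following dose reduction".

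**The concern.** Rows 2 and 3 are meant to be successive steps, but their triggers are not mutually exclusive. Persistence beyond 24 hours is one of the routes by which an asymptomatic rise becomes grade 2 at all, and it also appears to trigger row 3. The two actions cannot both be followed, because the drug is either continued or held.

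At stake is whether sites handle the same event alike. One site could keep a patient on uninterrupted full dose. Another could hold the drug, reduce it, and take the patient off protocol therapy if the hold exceeds two weeks. The conflict over re-escalation then leaves open whether a reduction for hypertension is ever reversible.

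**Working it through.** No design figure is involved, so the check is logical. All inputs come from section 5.2.

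**Setting up.** Describe a BP rise by four yes/no features: S (symptomatic), P (persistent, over 24 hours), R (recurrent), H (diastolic 110 mm Hg or more). By the printed definition a rise is grade 2 if S or P or R holds. Four features give 2^4 = 16 patterns. The two with S, P and R all absent are not grade 2, which leaves 14. Grade 3 is defined by treatment need and is left out.

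**Row conditions.**
- Row 2: not S, and not H.
- Row 3, slash as *or*: S or P or H.
- Row 3, slash as *and*: (S and P) or H.

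**Result for the 14 patterns.**

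| Reading of the slash | Row 2 only | Both rows | Row 3 only | No row |
| --- | --- | --- | --- | --- |
| *or* | 1 | 2 | 11 | 0 |
| *and* | 3 | 0 | 9 | 2 |

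Under *or*, the two double assignments are asymptomatic, persistent rises below 110, with or without recurrence. Only asymptomatic, recurrent, non-persistent rises below 110 fall in row 2 without conflict. Under *and*, the two unassigned patterns are symptomatic, non-persistent events below 110, with or without recurrence.

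**Timing.** An asymptomatic, non-recurrent rise stays grade 1 until it passes 24 hours, and row 1 calls only for considering more monitoring. The collision can therefore occur when grade 2 is first reached, before the table has asked for any anti-hypertensive.

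**Precedence.** The three footnotes cover delays over two weeks, later return to full dose, and more than two reductions. Neither they nor the rest of section 5.2 ranks the rows or defines *persistent* as persistent despite treatment.

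**The two orders in dose terms.** Row 2 keeps 400 + 400 = 800 mg/day without interruption. Row 3 holds the drug and then gives 400 + 200 = 600 mg/day, assuming that one dose level is the 200 mg/day step printed in the same section.

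**Re-escalation.** The row 3 footnote permits a return to full dose. The closing sentence covers all patients and names no exception. The two conflict for every row 3 reduction, including those for diastolic BP of 110 or more or for grade 3, so this defect exists independently of the overlap.

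**The case against.** The best defence is that the rows plainly escalate: monitor, treat and continue, hold and reduce, discontinue. A clinician would probably take *persistent* as persistent despite the treatment begun in row 2. The 24-hour reading leaves row 2 almost empty, which suggests that it was not intended. This is fair as to intent, and it makes the defect one of wording. It does not remove it, because the text prints a different meaning directly below the table and no other.

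A second defence is that the gap under *and* is partly covered, since section 5.2 opens by requiring other toxicity to be grade 0-1 before re-treatment. That stands to a degree: such events would lack a table row, but not all guidance. The general rule does not say whether to interrupt continuous dosing, start anti-hypertensives or reduce the dose.

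A third is that the hypertension footnote, being specific, overrides the general ban on re-escalation. That is a reasonable guess, but the ban is worded without exception.

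Some stronger inferences are tempting and not supported:

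- A reader might try to count affected patients from the earlier single-agent melanoma trial in section 2 (2 of 20 with hypertension needing intervention) or from the at-most-20% column of the adverse event list. Neither source gives symptoms, duration or diastolic BP, so neither measures or bounds this event.
- A reader might treat a row 3 reduction as permanent. The footnote says otherwise, so the point is unsettled.
- A reader might add the two-week hold limit here against the general three-week allowance. The former can stand as a stricter limit specific to hypertension, and the discontinuation rule tied to three weeks concerns grade 3 or 4 toxicity. This finding does not rest on it.

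**Conclusion.** The point holds as a wording defect in a dosing-safety instruction. With *persistent* taken as printed and the slash as *or*, one kind of grade 2 event receives two incompatible orders. With the slash as *and*, another kind has no table row. Neither reading makes the table complete and consistent. The re-escalation rules contradict each other on any reading of the slash.

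The consequence is confined to consistent dosing and safety handling. Both rows start anti-hypertensives. The documents give neither the frequency of the event nor any indication of how often sites would diverge, so no patient count is attached.

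A reader might infer that the response-rate test is compromised, but the documents do not support this. The two-stage design figures in section 11 do not depend on this table, and section 11.5 keeps eligible patients in the response analysis whatever their dosing deviations. A short clarifying amendment is warranted, and nothing larger.

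**What to change.** Reword the row 3 trigger as: grade 2 symptomatic, OR grade 2 persistent despite anti-hypertensive therapy (for example, diastolic BP still above 100 mm Hg at the next scheduled BP check after starting therapy), OR diastolic BP of 110 mm Hg or more, OR grade 3. The 100 mm Hg figure is the table's own control threshold. At presentation, row 2 then takes the 3 asymptomatic patterns below 110 and row 3 the other 11, with no overlap and no gap (3 + 11 = 14).

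The study calendar gives weekly BP in cycle 1 only. In later cycles vital signs fall on days 1 and 28, so the sponsor may prefer to state a number of days for the recheck.

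In the same amendment, settle re-escalation: either delete the footnote on resuming full dose, or add to the closing sentence of section 5.2 an exception for reductions made for hypertension under that footnote. Which rule to keep is a clinical decision for the sponsor.

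The cost is one reworded trigger and one deleted footnote or added clause. The wording as proposed adds no visits, procedures or patients; a fixed recheck interval could add a BP check.
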